### Outcomes and measures

2.5

The primary outcome was VAS pain scores in the immediate postoperative period (postoperative day 0 through 3). VAS scores were recorded by nursing staff, blinded to treatment group, every 6 h throughout the hospital stay. VAS scores on each postoperative day were averaged, and the daily averages were used for analysis. Secondary outcomes included postoperative opioid use, length of hospital stay, activity level during physical therapy, and knee range of motion. Total opioid consumption was calculated by converting opioids consumed to morphine equivalents. Length of hospital stay was calculated by measuring the time from the completion of surgery through discharge for each patient. Activity level during physical therapy was recorded by measuring the steps taken in daily physical therapy sessions. Knee range of motion was measured by the surgeon using a goniometer in the office at 3 weeks postoperatively.

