### Intraoperative interventions

2.3

Spinal anesthesia was induced with 3.0 mL 0.5% hyperbaric bupivacaine at the L3/4 interspaces (alternatively at the L2/3 or L4/5 interspaces). Sedation using propofol and intravenous fluid therapy during surgery was administered at the discretion of the anesthetist.

An epidural catheter was placed laterally at the L3/4 or L4/5 level using a 17-gauge Tuohy needle and inserted upward by 5 cm. A test dose of 1% lidocaine (50 mg) was initially injected, and the sensory block was tested after 10 min by applying ice to the ipsilateral thigh. Then, continuous epidural infusion for management of postoperative pain using the catheter that was inserted preoperatively for use during the TKA operation. 20 mL of 0.3% ropivacaine were administered and 0.2% ropivacaine was infused at 5 mL/h for 36 h.

Under ultrasound guidance as above, a 10-cm, 18-gauge Tuohy needle was introduced into the adductor canal. Following dilation of the adductor canal with normal saline, a 21-gauge nerve catheter was threaded up to 3 to 5 cm beyond the needle tip. The guidewire was removed upon the catheter exiting the needle tip while threading to avoid inadvertent advancement of the catheter out of the space. The catheter was then manipulated and normal saline injected to confirm the catheter tip location within the adductor canal on ultrasound visualization, with peri-arterial spread as the endpoint. Up to 5 to 10 mL of normal saline was used in total per catheter placement. 20 mL of 0.3% ropivacaine was then injected via the catheter, following which a continuous infusion of 0.2% ropivacaine commenced at 5 mL/h for 36 h and then removed.

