### Sample size calculation

2.6

The sample size calculation was based on a pilot study that we conducted on 20 patients. In this prior study, the mean difference and standard deviation of the VAS scores on postoperative day 0 between the ACB and EA groups were 0.42 and 0.21, respectively. From this, it was determined that 50 subjects would be required to reach an α value of 0.05 and a power of 90%. It was estimated that the attrition rate due to canceled surgery or reasons of late patient ineligibility could be up to 20% and, therefore, to account for this, the final sample size selected was n = 120 (60 per group).

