### Statistical analysis

2.7

Statistical analyses were conducted using SPSS v22.0 software (IBM, Chicago, IL). Conformity of the data to normal distribution was tested with the Kolmogorove–Smirnov test. Independent two samples *t* test was used for comparison of continuous variables and Pearson Chi Square test was used for comparison of categorical variables. Results were evaluated in a confidence interval of 95% and at a significance level of *P* < .05.

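### Four daily pain averages are primary with no deciding comparison, while the sample size rests on postoperative day 0 alone

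*Protocol article*

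**What the plan says.** Protocol article, section 2.5 (Outcomes and measures): "The primary outcome was VAS pain scores in the immediate postoperative period (postoperative day 0 through 3"). Readings are taken every 6 h during the hospital stay, and "VAS scores on each postoperative day were averaged, and the daily averages were used for analysis". Each patient therefore contributes up to four primary values.

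Section 2.7 (Statistical analysis) names the independent two-sample t test for continuous data: "test was used for comparison of continuous variables and Pearson Chi Square test was used for comparison of categorical variables". One threshold covers everything: "Results were evaluated in a confidence interval of 95% and at a significance level of *P* < .05".

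Section 2.6 (Sample size calculation) uses a single day. A pilot of 20 patients supplied both inputs, a difference in means and its SD, for POD 0 only: "scores on postoperative day 0 between the ACB and EA groups were 0.42 and 0.21, respectively". The section then states 50 subjects for an alpha of 0.05 and 90% power, raised to 60 per group for attrition.

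The Introduction and Discussion give the hypothesis that adductor canal block works as well as epidural analgesia. Section 2.2 keeps the randomization key closed until all enrolled patients have completed the study.

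**The concern.** An independent two-sample t test takes one value per patient. Section 2.5 supplies four and does not reduce them to one. A statistician following sections 2.5 and 2.7 would most naturally run four tests, one per day, each at 0.05. Nothing in the article ranks the days, combines them or says what happens if they disagree.

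Section 2.6 then treats POD 0 as if it were the endpoint, at an alpha that makes no allowance for other primary tests. The article thus carries two different ideas of its primary comparison: four days in one section and one day in the next.

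What is at stake is the main result. If one day is significant and three are not, the text permits either a report of a difference or a report of similar pain control, and the choice could be made after the results are seen.

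**Working it through.** **Inputs.** From the article: four daily averages (section 2.5); independent t test at 0.05 (section 2.7); POD 0 difference 0.42, SD 0.21, alpha 0.05, power 90%, 50 subjects, 60 per group (section 2.6). The 60 per group is 50 × 1.2, so 50 is read as per group. Assumed: two-sided tests (sidedness is not stated, but a 95% interval is) and a between-day correlation ρ from 0 to 0.9 (none is given).

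**Step 1: the plan's own figure.** n per arm = 2(z₀.₉₇₅ + z₀.₉₀)² × (SD/difference)² = 2 × (1.960 + 1.282)² × (0.21/0.42)² = 2 × 10.51 × 0.25 = 5.25, so 6 per arm (7 by the exact t calculation). The stated 50 does not follow from the stated inputs. That is a separate issue. It matters here only because the calculation shows which day was used and cannot show how much power any other day has.

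**Step 2: number of primary comparisons.** Four days × one test each = 4. Section 2.6 uses one of them.

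**Step 3: false-positive chance, independent days.** If any one significant day counts as a difference, 1 − (1 − 0.05)⁴ = 1 − 0.8145 = 0.185, or 18.5%.

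**Step 4: correlated days.** Daily pain averages in one patient will be correlated, which lowers this figure. Four correlated two-sample t tests were simulated with 50 per arm, no true difference and 100,000 trials per setting (simulation error about 0.1 percentage points).

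| Between-day correlation | At least one P < .05 |
|---|---|
| 0 (exact) | 18.5% |
| 0.3 | 17.3% |
| 0.5 | 15.7% |
| 0.7 | 13.1% |
| 0.8 | 11.5% |
| 0.9 | 9.5% |

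These rows assume equal correlation between all days. With correlation that decays with distance (AR(1)), the results are 16.8% at 0.5, 14.4% at 0.7 and 12.6% at 0.8.

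**Step 5: the opposite decision rule.** If similarity were claimed only when all four days are non-significant, the share of no-difference trials that pass would be 100% − 18.5% = 81.5% (independent days) to 100% − 9.5% = 90.5% (ρ = 0.9), against 95% for one test. The direction of the harm therefore depends on a rule that the article does not state.

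**Step 6: what splitting alpha would cost.** Bonferroni over four days gives 0.05/4 = 0.0125 per test. With 50 per arm, a standardized difference of 0.65 has about 90% power at 0.05 and about 77% at 0.0125. The family-wise rate is then 5.0% at ρ = 0 and 2.6% at ρ = 0.9.

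**The case against.** The strongest reply is that this is a condensed article. Section 2.7 is a short summary of generic methods, and a full analysis plan could hold a hierarchy or a longitudinal model. Neither section 2.5 nor section 2.7 says outright that four separate tests will be run or that any one significant day counts. The family-wise figures also concern falsely declaring a difference, while the stated hypothesis is similarity, for which the more harmful error is missing a real difference.

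Much of this stands. Per-day testing is an inference from joining two sections, the figures need an assumed correlation and an assumed decision rule, and the absence of a mixed model from an article is not itself an error. What does not fall away is the disagreement within the text: section 2.5 makes four days primary and section 2.6 sizes the trial on one. A plan that chose POD 0 would narrow section 2.5, and one that used a longitudinal model would replace the test in section 2.7. Either way this text needs correcting.

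A reader might also note that section 2.3 stops the adductor canal infusion at 36 h ("continuous infusion of 0.2% ropivacaine commenced at 5 mL/h for 36 h and then removed"), with the epidural infusion given the same duration. That reader might infer that the later days show little difference and so make similarity easy to claim. The documents do not support this. They give no expected difference for POD 2 or 3, section 2.5 deliberately includes those days, and under the rule in step 5 extra days make a similarity claim harder to reach.

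**Conclusion.** The point holds in limited form. The primary comparison is undefined across four daily averages, and the outcome definition does not match the basis of the sample size. Read together, the sections lead most naturally to one unadjusted t test per day. If any significant day is then taken as a difference, the chance of a false positive exceeds 5% throughout the range examined: 18.5% for independent days, about 16% at a correlation of 0.5, 13% at 0.7 and 9.5% at 0.9. These figures rest on three assumptions that the article does not state: per-day testing, the any-day rule and the correlation.

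Two stronger readings should be avoided. One is that the trial simply has a false-positive rate of 13% to 18%; that range applies only for correlations of about 0.2 to 0.7 and only under the any-day rule. The other is that POD 1 to 3 are underpowered. POD 0 was the basis of the calculation, but no inputs are given for the other days, so their power is unknown.

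The missing margin for the similarity hypothesis, and the 50 that does not follow from 0.42 and 0.21, are separate issues.

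**What to change.** Before unblinding, name one primary comparison and make sections 2.5, 2.6 and 2.7 agree on it. Two choices fit the text:

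- **The POD 0 average.** This is the day already used in section 2.6, and the t test in section 2.7 can stay.
- **One prespecified summary over POD 0 to 3** from a single repeated-measures model with arm, day and arm-by-day terms. This keeps the period that section 2.5 defines, but section 2.7 must name the model. Because readings are taken only during the hospital stay, it should also say how patients discharged before POD 3 are handled.

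In either case, restate the sample-size basis for the chosen comparison, since the present calculation does not reproduce. Report the remaining days as secondary, either as estimates with confidence intervals or tested in a fixed order.

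The change is to wording and analysis specification and needs no new measurements. The downside is that the remaining days lose primary status. Keeping all four days primary with a Bonferroni split is possible, but it carries the power loss shown in step 6 of the working.

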### Sample size calculation

2.6

The sample size calculation was based on a pilot study that we conducted on 20 patients. In this prior study, the mean difference and standard deviation of the VAS scores on postoperative day 0 between the ACB and EA groups were 0.42 and 0.21, respectively. From this, it was determined that 50 subjects would be required to reach an α value of 0.05 and a power of 90%. It was estimated that the attrition rate due to canceled surgery or reasons of late patient ineligibility could be up to 20% and, therefore, to account for this, the final sample size selected was n = 120 (60 per group).

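### The stated pilot inputs (difference 0.42, SD 0.21) give 7 patients per group, not the stated 50 subjects, so the 90% power is tied to no stated assumption

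*Protocol article*

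**What the plan says.** Section 2.6 (Sample size calculation) names its source: "The sample size calculation was based on a pilot study that we conducted on 20 patients". It reports that the mean difference and standard deviation of "the VAS scores on postoperative day 0 between the ACB and EA groups were 0.42 and 0.21, respectively". The next sentence presents the required number as the result of those two figures: "From this, it was determined that 50 subjects would be required to reach an α value of 0.05 and a power of 90"%. It does not say whether this is a total or a per-group number. After an allowance for attrition of up to 20%, "the final sample size selected was n = 120 (60 per group").

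Section 2.7 (Statistical analysis) names the test: "Independent two samples *t* test was used for comparison of continuous variables". The significance level is 0.05, with a 95% confidence interval. Sidedness is not stated. The article gives no other effect size, SD or margin.

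**The concern.** A difference of twice the standard deviation is very large, and detecting it takes a handful of patients per arm. A requirement of 50 is therefore out of proportion to the inputs from which it is said to come.

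This is the trial's only justification of its size. If its inputs and its result disagree, a reader cannot tell which difference the trial has 90% power to detect, or at what variability. That matters when a non-significant result has to be interpreted, because the SD decides how wide the confidence interval for the difference will be, and the SD is one of the figures in doubt.

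**Working it through.** **Inputs.** From section 2.6: difference δ = 0.42, SD σ = 0.21, α = 0.05, power 90%. From section 2.7: independent two-sample t test. Equal allocation follows from 60 per group. Two-sided testing is assumed, and one-sided is also tried.

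**1. Required number from the stated inputs.**
- Standardised difference: d = 0.42/0.21 = 2.0.
- Normal approximation: n per group = 2(z₀.₉₇₅ + z₀.₉₀)²/d² = 2(1.960 + 1.282)²/2.0² = 5.25, so 6 per group.
- Exact t test (noncentral t, 2n − 2 degrees of freedom, noncentrality d√(n/2)): power is 87.6% at 6 per group and 92.9% at 7. The requirement is 7 per group, 14 in total.

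The plan's figure of 50 is not reproduced.

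**2. Power at the stated number, same inputs.** At 25 per group (50 in total), power is 99.99997%. At 50 per group it is effectively 100%. Neither reading of 50 corresponds to 90%.

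**3. Other standard readings that keep the inputs as labelled.**
- One-sided 5% test: 5 per group (normal) or 6 (exact t).
- Bonferroni over four postoperative days (α = 0.0125): 8 per group (normal).
- 0.42 used as a non-inferiority margin: 6 per group (normal).

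None comes near 25 or 50 per group.

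**4. SD that would make the stated number correct (δ = 0.42, 90% power, exact t).**
- 50 per group: d = 0.655, so SD = 0.42/0.655 = 0.64, about three times the stated SD.
- 25 per group: d = 0.936, so SD = 0.42/0.936 = 0.45, about twice the stated SD.

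**5. Possible mislabelling of 0.21.**
- Standard error of one pilot arm, assuming the 20 patients were split 10 and 10: SD = 0.21 × √10 = 0.664. This needs 53.5, so 54 per group (exact t). It is close to 50 per group but does not equal it.
- Variance: SD = √0.21 = 0.458. With two-decimal z values, 2(1.96 + 1.28)² × 0.21/0.42² = 24.99, so 25 per group or 50 in total. With three-decimal z values it is 25.02, so 26 per group. The exact t test gives 26.02, so 27 per group (54 in total).
- Standard error of the difference, again assuming 10 and 10: SD = 0.21/√0.2 = 0.470. This needs 27 (normal) or 28 (exact t) per group.
- Difference and SD interchanged: 85 (normal) or 86 (exact t) per group.

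**6. Sensitivity of power to the SD (δ = 0.42, 50 per group, two-sided exact t).**

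| SD | Basis | Power |
|---|---|---|
| 0.21 | as stated | above 99.99% |
| 0.50 | between the implied values | about 99% |
| 0.64 | implied by 50 per group | 90% |
| 0.66 | 0.21 as the standard error of a 10-patient arm | 88% |
| 1.0 | assumption only, not in the document | 55% |

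**The case against.** The strongest reply is that the discrepancy errs on the safe side. On the stated inputs, 50 per group is far more than needed, and no figure in the document shows the trial to be too small. That stands. A reader might infer from the mismatch that the trial is underpowered, but low power appears only with SDs that the document does not give, such as 1.0. The analysed outcome is a daily average of 6-hourly scores (section 2.5), which tends to vary less than single scores, and at 60 per group power at SD 1.0 would be 63% rather than 55%. The reply does not remove the inconsistency, however: the trial is overpowered only if 0.21 is correct, and the 50 said to follow from it casts doubt on exactly that.

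A reader might also infer that 50 must be a per-group figure. The 60 per group (50 × 1.2 = 60) and the 100 patients in sections 2.1 and 2.2 favour this reading. But the text never says so, and a total of 50 may have been carried forward as a per-group number by mistake.

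It is equally tempting to conclude that 0.21 is really a standard error. That gives 54 per group, not 50. The variance reading hits 50 in total exactly under a two-decimal normal formula, yet it contradicts the printed label and leaves 60 per group unexplained. Neither can be established from the document.

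Finally, the hypothesis that the block is as effective as epidural analgesia might suggest that the error undermines a non-inferiority conclusion. No margin is stated, so nothing can be calculated on that point, and it adds no weight here.

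The condensed format of an article is no defence, because all five quantities are printed and they disagree.

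**Conclusion.** The concern holds as an internal arithmetic error. Taken as labelled, the inputs require 7 per group (14 in total), whereas the paragraph says 50. That is about 3.6 times too many if 50 is the total (50/14) and about 7 times if it is per group (50/7). At least one of the difference, the SD and the required number is misstated, and the 90% power cannot be traced to any assumption in the document.

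The result assumes a two-sided test with equal groups; a one-sided test changes 7 to 6 and nothing else. The implied SDs (0.64 for 50 per group, 0.45 for 50 in total) assume that 0.42 and 90% are correct. The document settles neither the cause of the error nor the trial's true power. Because this is the only basis given for the trial's size, and it fails on its own numbers, it should be corrected.

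**What to change.** - Go back to the pilot data and state whether 0.21 is a standard deviation, a standard error or a variance. Give the number of pilot patients per arm.
- State whether 50 is per group or in total, once the pilot data and the original calculation have been checked.
- Restate section 2.6 so that difference, SD, α, sidedness, power and n agree and can be reproduced with the test named in section 2.7.
- Report the resulting power for the number actually randomised over a range of SDs. The range should include those implied by the paragraph (about 0.45 to 0.66), with any larger value labelled as an assumption.

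The cost is a recalculation and one corrected paragraph. The stated power may turn out less favourable than 90%. The restatement itself needs no added patients; whether the trial's size is adequate is a separate question that can be judged only once the SD is known.

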### Study design and patient enrolment

2.1

Approval for the study was granted by the Changji Branch of the First Affiliated Hospital of Xinjiang Medical University (CJ97440). Written informed consent will be obtained from all of the participants. Prospective assessment will be done for 100 patients who are scheduled for unilateral primary TKA surgery in our academic hospital by a single senior surgeon between August 2020 and December 2021. Our study was registered in Research Registry (researchregistry5775) prior to the enrollment start. All surgeons, recovery room and floor nurses, research assistants, statisticians, and patients were blinded to group allocation. Only the anesthesiologists performing the blocks and operating room nurses were not blinded.

Inclusion criteria included the following: planned unilateral TKA; spinal anesthesia; American Society of Anesthesiologists physical status classification score of I to III. Exclusion criteria included the following: unwillingness to participate in the study; general anesthesia; contraindications for the application of ACB such as localized infection and neurological disease in the lower extremity; history of epilepsy; arrhythmia; alcohol or drug dependency; known allergy to local anesthetics; insufficient co-operation for the completion of the visual analog scale (VAS) for pain scores; patients who had an inability to communicate verbally or who were unwilling to give informed consent; American Society of Anesthesiologists physical status classification score of IV.

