### Randomization

2.2

Patients were randomized to ACB treatment or EA treatment by a computer random number generator. Every participant received a consecutive study number from 1 to 100 and received the treatment assigned according to the randomization list. The randomization key was first broken when all enrolled patients had completed the study (Fig. 1).

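### The allowance for 20% attrition was computed as 50 × 1.2 = 60 per group; keeping 50 per group at that attrition needs 50 / 0.8, that is 63 (a minor correction)

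*Protocol article*

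**What the plan says.** Section 2.6 (Sample size calculation) of the protocol article gives the whole chain in one paragraph.

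- **Effect inputs**, from a pilot study in 20 patients: the mean difference and "standard deviation of the VAS scores on postoperative day 0 between the ACB and EA groups were 0.42 and 0.21, respectively".
- **Requirement:** "it was determined that 50 subjects would be required to reach an α value of 0.05 and a power of 90" per cent. It does not say whether the 50 is per group or in total.
- **Attrition:** "It was estimated that the attrition rate due to canceled surgery or reasons of late patient ineligibility could be up to 20" per cent.
- **Result,** offered as the number that allows for this attrition: "the final sample size selected was n = 120 (60 per group").

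The step from 50 to 60 is not shown.

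Other sections give a different total. Section 2.1 says "Prospective assessment will be done for 100 patients who are scheduled for unilateral primary TKA surgery", the Abstract gives the same number, and section 2.2 says "Every participant received a consecutive study number from 1 to 100".

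**The concern.** An attrition rate is the share of enrolled patients who are lost. To end with a required number, that number is divided by the share retained. Multiplying it by one plus the rate adds 20% of the smaller, evaluable number and always falls short. The move from 50 to 60 looks like the second calculation.

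At stake is whether the plan protects the number it declares it needs. Section 2.6 presents 60 per group as sufficient for attrition of up to 20%. If 60 falls below 50 at that rate, the statement is wrong on its own terms, and anyone who relies on it for recruitment or for reporting the sample size will believe there is more cover than there is.

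**Working it through.** **Inputs, all from section 2.6:** requirement N = 50; attrition d = 0.20; final size 60 per group, 120 in total.

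**Step 1. Is the 50 per group or in total?**

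- As a total, it is 25 per group. Then 25 × 1.2 = 30 and 25 / 0.8 = 31.25, so 32. Neither gives 60.
- As a per-group figure, the total is 100, which matches the Abstract and sections 2.1 and 2.2, and the move to 60 per group can be explained.

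Per group is therefore taken as the reading. It is an inference, because the text does not label the number.

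**Step 2. Reproduce the plan's figure.**

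N × (1 + d) = 50 × 1.2 = 60 per group, 120 in total. This is an exact match.

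**Step 3. The allowance that keeps 50 at 20% loss.**

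N / (1 − d) = 50 / 0.8 = 62.5, rounded up to 63 per group, 126 in total. Check: 63 × 0.8 = 50.4, which is at least 50. Working on the total instead, 100 / 0.8 = 125, which is also not 120.

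**Step 4. What 60 per group delivers.**

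| Quantity | Calculation | Result |
|---|---|---|
| Evaluable per group at 20% loss | 60 × 0.8 | 48 |
| Shortfall against 50 | 50 − 48 | 2 per group |
| Largest attrition that keeps 50 | 1 − 50/60 | 16.7% |
| Extra patients for full 20% cover | 126 − 120 | 6 in total |

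**Step 5. Can this be turned into a loss of power?**

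Only under an assumption that the document does not make. Suppose that 50 per group gives exactly 90% power with a two-sided t test at α = 0.05. The standardised difference that this implies is d = 0.655. At that effect, 48 per group gives 88.8% power, a loss of about 1.2 percentage points.

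The printed inputs point elsewhere. With 0.21 read as the between-patient standard deviation, d = 0.42 / 0.21 = 2. The normal approximation, two-sided, gives

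n = 2 × (1.960 + 1.282)² / 2² ≈ 5.3, so 6 per group;

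the t test needs 6.4, so 7 per group. Power at 48 per group is then practically 100%. Other readings do not give 50 either: a one-sided test needs 5 per group, exchanging the two values needs 85, and treating 0.21 as the standard error of the pilot difference with 10 per arm (an assumed split) needs 27.

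The shortfall in patients thus follows from the plan's figures. The power figure of 88.8% does not.

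**The case against.** Four points can be made for the plan.

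1. **The 50 is not labelled.** Read literally as a total, it is far exceeded by the 120 × 0.8 = 96 patients left at 20% loss, and nothing is short. This stands as a reason to state the per-group reading as an assumption. It does not remove the point, because a total of 50 cannot be connected with 60 per group by a 20% allowance.
2. **The rate is a ceiling.** If actual attrition stays at or below 16.7%, at least 50 per group remain. That is true, but the allowance is offered as cover for losses up to the ceiling, and it fails there.
3. **The shortfall is trivial.** Two patients per group are unlikely to change any conclusion of the trial. This stands, and it sets the severity.
4. **Correcting this sentence alone leaves larger problems.** The Abstract and sections 2.1 and 2.2 plan for 100 patients. If 100 are enrolled and 20% are lost, 100 × 0.8 / 2 = 40 per group remain, a wider gap than 48 against 50. The base of 50 also does not follow from 0.42 and 0.21. This stands too, and the remedy has to take it into account.

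A reader might also infer that the trial is underpowered, or that its power at 20% attrition is 89% rather than 90%. The document does not support that. The 89% rests on an effect of d = 0.655, which is found only by assuming that the 50 is right and which conflicts with the printed difference and standard deviation.

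**Conclusion.** The point holds as an inconsistency in numbers of patients. Taking 50 as per group, 60 per group leaves 48 at the plan's own 20% attrition, 2 per group below its own requirement. The correct allowance is 63 per group (126 in total), and 60 covers losses up to 16.7%. The exact match with 50 × 1.2 makes the source of the slip plain.

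The severity is minor. The conclusion rests on one assumption, the per-group reading, which is well supported but not stated. The arithmetic does not depend on how the 50 was obtained. Any statement about power does, so none can be made for 48 per group until that number is justified.

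**What to change.** In section 2.6, label the 50 as per group, if that is what is meant, and then do one of the following:

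- keep 60 per group (120) and say that it preserves 50 evaluable per group for attrition up to 16.7%, with 48 per group remaining at 20%; or
- give 63 per group (126) as the enrolment figure, if cover for the full 20% is to be claimed.

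Do not add a power figure for 48 per group at this stage.

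In the same revision, reconcile the 120 in section 2.6 with the 100 patients in the Abstract and section 2.1 and the study numbers 1 to 100 in section 2.2, and show how the 50 was derived from the pilot inputs. Otherwise the corrected sentence would still stand in an inconsistent sample size plan, and 126 would widen the gap to 100.

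The attrition sentence itself costs nothing but a rewording if 60 is kept: design and conduct stay as they are, and the stated cover becomes slightly less favourable. Going to 63 costs 6 more patients than the 120 now stated. Reconciling 100 with 120 and justifying the 50 take more work, but both are needed in any case.

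### The sample size section selects 120 patients (60 per group), but enrolment is planned for 100 and participants are numbered 1 to 100; on the likely reading of the requirement, 100 leaves no allowance for attrition

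*Protocol article*

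**What the plan says.** The protocol article gives the size of the trial in four places.

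- **Abstract (Methods) and section 2.1, Study design and patient enrolment:** "Prospective assessment will be done for 100 patients who are scheduled for unilateral primary TKA surgery in our academic hospital".
- **Section 2.2, Randomization:** "Every participant received a consecutive study number from 1 to 100 and received the treatment assigned according to the randomization list".
- **Section 2.6, Sample size calculation:** the requirement is put as "50 subjects would be required to reach an α value of 0.05 and a power of 90" per cent. The article then estimates that "the attrition rate due to canceled surgery or reasons of late patient ineligibility could be up to 20" per cent, and to cover this "the final sample size selected was n = 120 (60 per group").

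The inputs to the requirement are also in section 2.6. They come from a pilot study of 20 patients, in which the mean difference and standard deviation of day 0 VAS scores "between the ACB and EA groups were 0.42 and 0.21, respectively". The section does not say whether the 50 subjects are per group or in total, what the 0.21 is the standard deviation of, or whether alpha is one-sided or two-sided.

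**The concern.** A trial needs one prespecified size, and this one states two. Stopping at 100 could be reported as following the plan or as falling 20 patients short of it. Continuing to 120 would need study numbers that section 2.2 does not provide. Section 2.2 also ties the breaking of the randomisation key to completion by all enrolled patients, so the timing of that event depends on which size applies.

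The second issue is the attrition allowance. Section 2.6 raises the requirement to cover losses, but the enrolment figure elsewhere does not carry that increase. If 50 is a per-group figure, 100 patients is the requirement before any loss, and any loss among them takes the trial below it.

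**Working it through.** **1. The counts side by side**

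| Place | Size |
|---|---|
| Abstract (Methods) | 100 |
| Section 2.1 | 100 |
| Section 2.2 | study numbers 1 to 100 |
| Section 2.6 | 120 (60 per group) |

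The difference is 120 − 100 = 20 patients, or 20/120 = 17% of the larger figure.

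**2. Reproducing the 120**

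50 × 1.2 = 60 per group, and 2 × 60 = 120. This works only if 50 is per group, so that reading is implied by the arithmetic although the text does not state it. Multiplying by 1.2 is also slightly short: 60 × 0.8 = 48 per group remain after a 20% loss. Keeping 50 would need 50/0.8 = 62.5, so 63 per group.

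**3. What 100 leaves**

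With no loss, 100/2 = 50 per group. With the full 20% loss, 100 × 0.8 = 80, or 40 per group.

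**4. Reproducing the 50**

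Inputs from section 2.6: difference 0.42, SD 0.21, alpha 0.05, power 90%. Two-sided alpha is my assumption. The standardised effect is d = 0.42/0.21 = 2.0.

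n per group = 2(z₀.₉₇₅ + z₀.₉₀)²/d² = 2 × (1.960 + 1.282)²/4 ≈ 5.3, so 6 per group. The exact t-test calculation gives 7 (6 if one-sided).

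Other readings of the inputs do not give 50 either:

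- Difference and SD exchanged: 85 per group (69 one-sided).
- 0.21 as the standard error of the difference, assuming 10 pilot patients per group, so SD = 0.21/√(2/10) = 0.47: 27 to 28 per group, 54 to 56 in total.
- 0.42 as a standardised effect: 120 per group.

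The stated 50 is therefore not reproduced.

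**5. Power at the possible sizes**

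The answer depends on which part of section 2.6 is trusted. The normal approximation is Φ(d√(n/2) − 1.960).

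*Stated inputs, d = 2.0.* At 40 per group: Φ(2 × √20 − 1.960) = Φ(6.98), above 99.99%.

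*The claim that 50 per group gives 90%, taken at face value.* The implied effect is d = 3.242 × √(2/50) = 0.648 by the normal approximation, or 0.655 by the t test. At 40 per group the normal approximation is Φ(0.648 × √20 − 1.960) = Φ(0.94) = 82.6%. The t-test figures are:

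| Evaluable per group | Arises from | Power |
|---|---|---|
| 40 | 100 enrolled, 20% lost | 82.4% |
| 48 | 120 enrolled, 20% lost | 88.8% |
| 50 | 100 enrolled, no loss | 90.0% |
| 60 | 120 enrolled, no loss | 94.5% |

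*50 as a total (25 per group) giving 90%.* The implied d is about 0.92, and 40 per group gives about 98%.

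**The case against.** The strongest objection concerns power. A reader might infer that running the trial at 100 takes power below the stated 90%. The article does not support that as a flat statement. It needs three things together: that 50 is per group, that 50 per group really gives 90%, and that the full 20% is lost. The first is inferred. The second conflicts with the 0.42 and 0.21 in the same section. The third is given only as an upper limit, and with no loss 100 patients keep whatever power 50 per group has. This objection stands, and the 82% must remain conditional.

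A second objection is that 120 might be recruited and about 100 numbered and treated, since the named losses (cancelled surgery and late ineligibility) largely fall before treatment. Taking a further 20% off 100 would then count attrition twice. The article does not say this. Section 2.1 applies 100 to patients scheduled for surgery, section 2.2 numbers every participant up to 100, and section 2.6 calls 120 the final size and splits it by group. The timing of losses does affect how many evaluable patients 100 would yield, so 40 per group is the lower end of the plan's own range and not a forecast.

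Third, the risk of data-driven stopping is limited. No interim analysis is described, statisticians and the nurses recording pain scores are blinded, and the key is broken only after all patients complete. That is fair and reduces the harm, but it does not settle which number ends recruitment.

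Condensation into an article does not explain the conflict, because the problem is two stated sizes and not a missing detail.

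**Conclusion.** The contradiction between 120 and 100 holds without any assumption and needs correcting. The sample size is wrong as written in at least one place, and patients 101 to 120 have no study number.

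The loss of the attrition allowance holds if 50 is per group, which is the only reading that reproduces 60 per group. On that reading, a full 20% loss from 100 leaves 40 per group against a requirement of 50.

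The effect on power cannot be given as one number. It is about 82% at 40 per group if 50 per group is taken to give 90%, and above 99.99% if the stated difference and SD are used. That spread shows that the inputs in section 2.6 do not support the 50 derived from them; it is not evidence that 100 patients are enough. All power figures assume a two-sided alpha of 0.05 and a test for a difference.

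**What to change.** Choose one sample size and use it in the Abstract, section 2.1, section 2.2 and section 2.6.

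- **If 100 is kept:** delete the 120 (60 per group) from section 2.6, together with the claim that attrition is covered.
- **If 120 is the target:** change the Abstract and section 2.1, and extend the study numbers and the randomisation list to 120 before more patients are entered.

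In either case, state in section 2.6 whether 50 is per group or in total, what the 0.21 is the standard deviation of, and whether alpha is two-sided. Then recalculate the power at the chosen size and expected attrition from the reconciled inputs. Do not enter 82% as a fixed figure, since the inputs now printed in the same section contradict it.

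Allocating study numbers only once surgery and eligibility are confirmed would limit the losses the article names. This is optional, because the article does not say when patients are randomised.

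The cost is a short amendment and possibly a less favourable stated power.
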